Demonstrate non-inferiority of a stepped-care model of DP after short IP stabilisation versus full-time IP based on BMI at 12 months post-randomisation (primary outcome).Demonstrate non-inferiority of a stepped-care model of DP after short IP stabilisation in term of clinical, biological outcomes, AN symptoms, comorbidities, and relapse at different time points (weight normalization, 6, 12 months).Assess the impact of a stepped-care model of DP after short IP stabilisation versus full-time IP on treatment satisfaction and quality of life of patients and parents at 6 and 12 months.Assess the impact of the prospect of discharge to DP on initial IP (duration before somatic stabilisation, motivation to change) at inclusion and somatic stabilisation.Determine factors associated with positive response to stepped-care model of DP after short IP.Determine the cost-utility and cost-effectiveness of a stepped-care model of DP after short IP stabilisation compared with full-time IP.

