### Procedure (Fig. 1)

**Fig. 1 Fig1:**
[figure not shown]
Study flowchart

At initial clinical assessment, eligible children and caregivers will be informed of the study and study protocol is fully explained by the investigator. After signature of the informed consent by the holder(s) of parental authority, target weight for weight normalisation will be calculated and participants will be randomised into one of the two trial arms. Weight normalisation is individualised and will be determined at inclusion and before randomisation to return to the previous BMI growth trajectory and is calculated by two different investigators [15–18].

Randomisation will be done by a randomisation list with the nQuery Advisor and nTerim 4.0 software implemented in the eCRF. Children and parents are informed of the result of the randomisation by the investigator.

After inclusion and randomisation, participants will be managed in 3 phases:

*period 1: *Full-time IP until somatic stabilisation (see below for definition); *period 2:* DP or IP according to their randomisation arm until weight normalisation is reached; *period 3:* OP follow-up.

*Period 1: *Full-time IP—identical for all included children- ongoing until somatic stabilisation, which is defined as: BMI over the 3^rd^ percentile, disappearance of somatic severity criteria for undernutrition such as bradycardia (heart rate below 40 per minute during sleep time or below 50 per minutes during day time), persistent disturbances of the biological balance (hypoglycaemia, hypophosphoremia, haemolysis, cytolytic hepatitis, elevated creatine kinase), or any somatic or biological manifestation requiring constant surveillance in hospital with usual medical, dietary and psychological care (persistent refusal to drink or eat, lipothemia, hypothermia). The treatment provides multi-disciplinary care for the child and his/her family as described in French guidelines [14], including:Child follow-up of AN and psychiatric comorbidities by a senior psychiatrist on a bi-weekly basisEndocrinologic and somatic evaluation by a senior endocrinologic paediatric for initial assessment M6 and M12 and by a psychiatrist resident for follow-up during IP and by a general practitioner during OPNutritional monitoring with a bi-weekly dietetic follow-upPsychological follow-up with weekly family therapyTherapeutic education for the child with a weekly psychoeducation group and day-care nurse follow-up

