We will target a rapid weight gain from 500g to 1.5kg a week depending on the tolerance [19].

*Period 2: *At the end of the first period, patients start to receive treatment according to their randomisation arm until the weight normalization is reached. *For the control group*, full-time IP is continued as described in period 1 with additional cognitive remediation weekly group and weekly individual cognitive-based therapy until the weight normalisation is reached. During this time period, IP patients can benefit from permission to go home twice a week on Wednesday afternoons and weekends. *For the experimental group*, participants are discharged from IP and switch to DP one day per week until weight normalisation is reached.

The standardized DP treatment combines a medical assessment by a senior psychiatrist, family oriented treatment (parents' group and multi-family therapy session), a psychoeducation group, a cognitive remediation group, a dietetic follow-up with therapeutic meals and body constants monitoring (heart rate and blood pressure). Patients in the experimental group can return to their school activities and home life. During this period, the number of individual cognitive-based therapy sessions out from the hospital will be reported. If absence of weight gain leading to a BMI < 3rd percentile or weight loss of more than 10% of body weight during DP, patient will be readmitted to full-time IP until the weight normalisation is reached.

*Period 3: *After weight normalisation is reached, all patients will be provided the same OP follow-up until 12 month with a psychiatric consultation every month for 3 months and then once every 2/3 months as proposed in usual care.

Clinical, biological and psychometric assessments are done at baseline, at somatic stabilisation, at reaching weight normalisation, at 6 months and 12 months following study inclusion.

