#### Statistical analysis plan

The statistical analysis of the data will be performed using an intention-to-treat analysis, all patients allocated to the control group or experimental group will be analysed. The descriptive analysis for each group at each assessment time will be expressed as number (percentage) for categorical variables, and as mean (SD) or Median [IQR] according to their normal or non-normal distribution for quantitative variables. As described above, the primary outcome for non-inferiority analysis is based on the comparison of the BMI at 1 year after inclusion between the two groups with a two-sided 95% confidence interval. Experimental strategy will be considered as non-inferior if the confidence interval upper limit of the difference in BMI between the 2 groups is less than 1 kg/m^2^ (non-inferiority margin) with a 0.025 alpha risk. The comparative analysis between the 2 groups for the primary or secondary criteria will be carried out using the appropriate tests: Chi^2^ test or Fisher's exact test for qualitative variables; Student's t test or non-parametric Wilcoxon test for quantitative variables, according to their normal or non-normal distribution. To determine prognosis factors associated with positive response to stepped-care model of DP after short IP, a regression model will be used to search for factors associated with the effect of the intervention, integrating the MRS score as the explained variable, and the CGI score, the HAQ11 and motivation questionnaire scores, and the severity of the weight deficit as explanatory variables.

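### Objective 4 compares time to somatic stabilisation without adjusting for each child's starting weight gap to the 3rd-percentile limit: valid, but less precise than the data already collected allow (minor)

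*Protocol article*

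**What the plan says.** - **Objective (Background, fourth specific objective).** The trial will assess the impact of the "prospect of discharge to DP on initial IP (duration before somatic stabilisation, motivation to change" at inclusion and stabilisation. No covariate, scale or target effect is given for the duration.
- **What ends the duration (Methods, Procedure, Period 1).** The weight part and the first clinical part are "BMI over the 3^rd^ percentile, disappearance of somatic severity criteria for undernutrition such as bradycardia". Biological disturbances must also have resolved, as must "any somatic or biological manifestation requiring constant surveillance in hospital with usual medical, dietary and psychological care".
- **Rate of gain (same section).** "We will target a rapid weight gain from 500g to 1.5kg a week depending on the tolerance".
- **Why allocation could act in period 1.** Care in this phase is "identical for all included children", but randomisation comes before it and "Children and parents are informed of the result of the randomisation by the investigator".
- **Test (Data analysis, Statistical analysis plan).** Primary and secondary criteria are compared by "Student's t test or non-parametric Wilcoxon test for quantitative variables", the choice depending on normality. The degree of weight deficit appears as a covariate only in the regression of the Morgan and Russell score for objective 5.
- **Data (Table 1).** Weight, height and BMI are recorded at inclusion and at stabilisation.

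**The concern.** The duration runs from inclusion to a date set in part by a fixed weight limit. A child 4 kg below that limit needs twice the time of a child 2 kg below it at the same rate of gain. Knowing that day care will follow may change how fast a child gains, or how soon other signs clear. It cannot change the gap at inclusion. A test of arm alone leaves the variation due to that gap in the error term.

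With 44 children per arm, a real shortening of period 1 could be missed that the same data would show after adjustment. The objective bears on the trial's interest in shorter hospital stays, and the adjustment needs no new measurement.

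**Working it through.** **The plan's own figure.** No sample size or power is stated for objective 4. The only one is for the primary outcome: margin 1 kg/m², SD 1.35, one-sided 2.5%, power 90%. The normal formula gives 2 × 1.35² × (1.960 + 1.282)² / 1² = 38.3, so 39 per arm. The noncentral t version gives 40 per arm (power 90.5%), which matches the stated 80. This point does not affect it.

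**Step 1: how the gap enters the duration.** Write duration ≈ max(gap / rate, time for other signs to clear), with gap = (3rd-percentile BMI − inclusion BMI) × height². The rate range of 0.5-1.5 kg/week is from the protocol. Dividing the gap by the rate:
- 2 kg gap: 28, 14 and 9 days at 0.5, 1.0 and 1.5 kg/week.
- 4 kg gap: 56, 28 and 19 days.

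Gap and rate therefore both matter. The stated rates alone spread the same gap over a threefold range of days.

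**Step 2: what adjustment can gain in principle.** With 44 per arm, two-sided 5% and 80% power, the detectable difference is √(2/44) × (1.960 + 0.842) × √(1 − R²) in SD units. R² is the share of variance explained by the gap.
- R² = 0: 0.60 SD
- R² = 0.25: 0.52 SD
- R² = 0.50: 0.42 SD
- R² = 0.75: 0.30 SD

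**Step 3: simulated power.** The following are assumptions, because the documents give none of them: height 1.45 m (SD 0.08), 3rd-percentile BMI 14, mean inclusion BMI 12.8 with SD 0.5, 0.8 or 1.0, and rate uniform over 0.5-1.5 kg/week. The mean gap is then about (14 − 12.8) × 1.45² = 2.5 kg. The true effect is 25%, applied either to the whole duration or only to the time needed to gain the weight. Other signs clear in 0.5-2, 1-4 or 1-6 weeks. This makes 3 × 2 × 3 = 18 cells, with 1,500-2,000 simulated trials each. Powers below are in order of BMI SD 0.5/0.8/1.0.

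- *Other signs 0.5-2 weeks.* Effect on whole duration: t test 75/57/47%, Wilcoxon 76/57/48%, linear model of untransformed duration on arm and gap (ANCOVA) 97/95/93%. Effect on weight gain only: t test 65/46/39%. Gain from ANCOVA: about 20-45 points.
- *Other signs 1-4 weeks.* Effect on whole duration: t test 95/83/74%, Wilcoxon 96/90/84%. Effect on weight gain only: t test 43/36/34%, with ANCOVA at 53% for SD 0.8. Gain: about 4-22 points.
- *Other signs 1-6 weeks.* Effect on whole duration: t test 97/93/89%, ANCOVA 97-98%. Effect on weight gain only: every test is near 16-25%. Gain: about 1-9 points.

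ANCOVA on untransformed duration was at or above both unadjusted tests in all 18 cells. The gap explained roughly 15-75% of the variance of log duration.

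**Step 4: scale.** A log-duration model with the same covariate does best when other signs clear fast. It falls behind untransformed ANCOVA in most of the less favourable cells. For example, it gives 42% against 53% with other signs at 1-4 weeks, effect on weight gain only, SD 0.8.

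**Step 5: validity.** With no true effect, the unadjusted t test rejects in 4.96% of trials (gap uniform over 1-5 kg, other signs ignored). Null runs under the Step 3 model also stay near 5%.

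**The case against.** The strongest reply is that nothing here is wrong. Randomisation precedes period 1, so the gap is balanced in expectation and the unadjusted comparison is unbiased. The statistical section is a summary in a journal article, and covariate adjustment of one secondary outcome often sits in a plan that is not shown. Other criteria, such as bradycardia, biological disturbance or refusal to eat, can decide the date. The size of the gain then depends on assumptions about how fast they clear.

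Most of this stands, and it limits the point. It does not remove it: the article names the unadjusted tests for secondary criteria, and adjustment was no worse than those tests in any cell tried.

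Stronger readings are tempting but not supported:
- *A reader might infer that the starting deficit largely fixes the duration and hides any effect.* The stated gain target spans threefold, several non-weight criteria also apply, and the gap's share of variance may be as low as about 15%.
- *A reader might infer that chance imbalance in starting weight makes the test misleading.* In trials where one arm happens to start with a clearly smaller deficit (at least 1 SD of chance imbalance), the null rejection rate does rise, to about 7-18%. Averaged over all randomisations it is still 5%, which is what the test promises.
- *A reader might expect power near 100% after adjustment.* That holds only if other signs clear quickly or if allocation shortens every component of the duration. If it acts on weight gain alone and other signs take 1-6 weeks, no analysis does well.

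**Conclusion.** The point holds as a minor matter of efficiency. The stated test ignores a baseline quantity that, by the trial's own definition of stabilisation, helps determine the outcome. The comparison remains valid, and what is lost is precision.

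The loss ranges from negligible (about 1 power point) to substantial (about 45 points). Where it falls depends chiefly on how long the non-weight signs take to clear, then on the spread of inclusion BMI and on which part of the duration allocation affects. The documents give none of these, so no single figure should be quoted.

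**What to change.** For objective 4, replace the unadjusted test of duration with a linear model (ANCOVA) of period-1 duration on arm and inclusion gap. Define the gap as the 3rd-percentile BMI for age and sex times height squared, minus inclusion weight, set to 0 if negative. Use robust or bootstrap confidence limits if residuals are skewed, and report raw medians by arm as description.

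Keep the untransformed scale rather than logs, for the reason in Step 4. Weight gain per week in period 1 is not a good substitute. It is measured over a window whose end depends on the weight reached, so it does not cleanly remove the starting deficit.

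The cost is one sentence in the analysis plan, fixed before the data are compared by arm. Weight and height at inclusion are already scheduled. Age, sex and the percentile reference are needed anyway to apply the stabilisation definition.

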**Methods:**

Eighty-eight children aged 8 to 13 years suffering from EOAN with initial severe undernutrition will be randomly allocated to either IP treatment as usual or a stepped care DP model both targeting weight normalization. Assessments will be conducted at inclusion, somatic stabilization, weight normalization, 6 months and 12 months post randomisation. The primary outcome will be BMI at 12 months post-randomisation. Secondaries outcomes will included clinical (tanner stage), biological (prealbumin, leptin, total ghrelin and IGF1) and radiological (bone mineralization and maturation) outcomes*,* eating symptomatology and psychiatric assessments, motivation to change, treatment acceptability and quality of life assessments, cost-utility and cost-effectiveness analyses.

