### Measures (Table 1)

**Table 1 Tab1:** Overview of measures and time of assessment

Assessment	Inclusion	Stabilisation	Weight normalization	6 months	12 months
*Clinical assessment weight, height, BMI *	x	x	x	x	x
tanner stage	x			x	x
*Nutritional markers* prealbumin, leptin, total ghrelin and IGF1	x		x		x
*Radiology* Bone mineralization (dual-energy X-ray absorptiometry) Bone maturation (en face radiograph of the left wrist)	x				x
*Global psychosocial* CGI	x		x	x	x
*Eating symptomatology* EDI-c, MRS	x		x	x	x
*Anxiety and depressive symptomatology* CDI, STAIC	x		x	x	x
*Self-esteem Scale* Rosenberg	x		x	x	x
*Motivation to change* HAQ-11S, Motivation questionnaire	x		x	x	x
*Treatment acceptability and quality of life* CSQ-8, SF-12	x		x	x	x
Resource consumption		x	x	x	x

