*Depressive and anxiety symptomatology* will be respectively assessed by the Children Depression Inventory (CDI) [24], the *State –Trait Anxiety Inventory for Children* (STAIC) [25]. The CDI is a self-adapted Beck Depression Inventory for children aged 7 to 17 years, with 27 items scored from 0 (absent or normal behaviour for age) to 2 (severe). The total score, calculated as the sum of all the items, varies from 0 to 54 with a pathological threshold of 15. It is a widely used tool in the international literature to assess the intensity of depression.

The STAIC is a self-questionnaire and comprises two 20-item subscales, the Trait Anxiety and the State Anxiety. The scores observed for the two subscales range from 20 to 80, with a score of 35 or less corresponding to very low anxiety and a score of over 65 corresponding to very high anxiety.

*Self-esteem will be assess by the Rosenberg Self-esteem Scale * [26]* is* a self-questionnaire with a 10-items measure of global self-esteem, widely used in general and clinical populations. The higher the scores, the better the self-esteem. It can be used from the age of 8 years.

*Therapeutic alliance/perception of treatment benefit and Motivation to change* will be assessed by the *Helping Alliance Questionnaire-11* (HAQ-11S) [27], the *Consumer Satisfaction Questionnaire* (CSQ-8) [27] and the *Motivation Questionnaire* [28].

The CSQ-8 is a self -"satisfaction"-questionnaire, defined here as a concept tending to assess whether the needs of the consumer of a service are being met or not. In medical terms, patient satisfaction is an internationally recognized measure for the evaluation of the perception of quality of care; this dimension can have an influence on the outcome and adherence to the proposed treatment and thus on the acceptability of the treatment. It consists of eight questions, each with four response options ranging from one "not at all satisfied" to four "completely satisfied".

The HAQ-11S is a self-questionnaire of 11 items measuring the strength of the collaboration between the patient and the healthcare team.

The Motivation Questionnaire will assess the importance of change and the perceived ability to change. It consists of two questions: "How important is it for you to change" and "How confident are you in your ability to change". Both questions are rated on a Likert scale from 0: "Not at all" to 10: "Completely".

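### Table 1 leaves motivation to change blank at somatic stabilisation, although the fourth objective names that time point and the Procedure text says psychometric assessments are done there

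*Protocol article*

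**What the plan says.** Three places in the protocol article set the timing of the motivation measurement, and a fourth lists the visits.

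- **Background, fourth specific objective.** The effect of the prospect of moving to day care is to be assessed "on initial IP (duration before somatic stabilisation, motivation to change) at inclusion and somatic stabilisation". This fixes two endpoints and names stabilisation as a time point.
- **Measures, Table 1** ("Overview of measures and time of assessment"). The motivation row, "HAQ-11S, Motivation questionnaire", is marked at inclusion, weight normalisation, 6 months and 12 months. The stabilisation cell is empty.
- **Procedure, closing sentence.** "Clinical, biological and psychometric assessments are done at baseline, at somatic stabilisation, at reaching weight normalisation, at 6 months and 12 months". No instrument is named.
- **Abstract, Methods.** "Assessments will be conducted at inclusion, somatic stabilization, weight normalization, 6 months and 12 months post randomisation". This confirms that stabilisation is a visit but does not say what is measured there.

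The instrument is described under Secondary outcomes: "The Motivation Questionnaire will assess the importance of change and the perceived ability to change". It has two questions, each rated 0 to 10, and that section gives no timing.

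**The concern.** The objective concerns an expectation. Families learn their allocation at the start, while care during period 1 is the same in both arms. A difference between arms in motivation at the end of period 1 can therefore be read as an effect of knowing that discharge to day care lies ahead. Once period 2 begins, one arm is at home and back at school with a weekly day at the hospital, and the other continues full-time inpatient care. A later difference mixes the expectation with the care itself.

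Stabilisation is thus the time point on which the motivation part of the objective depends, and it is the one that Table 1 leaves empty. A self-report of motivation at that moment cannot be reconstructed afterwards.

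**Working it through.** No figure in the plan depends on this point, so the check is a comparison of the texts.

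**Step 1: align the motivation row of Table 1 with its header and compare it with the other statements.**

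| Source | Inclusion | Stabilisation | Weight normalisation | 6 months | 12 months |
|---|---|---|---|---|---|
| Fourth objective (motivation) | yes | yes | not named | not named | not named |
| Table 1, motivation row | x | blank | x | x | x |
| Procedure, closing sentence (psychometric) | yes | yes | yes | yes | yes |

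The objective and the Procedure sentence agree on stabilisation. Table 1 is the outlier.

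**Step 2: ask whether the blank could be a fault of text extraction.** The last row, "Resource consumption", is blank at inclusion and marked at the four later times, which is the sensible pattern for that item. Its marks have not slid to the left. The motivation row has four marks with the gap in the second position, the same pattern as the other five questionnaire and rating-scale rows. The blank therefore looks like part of the table.

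**Step 3: see what Table 1 does schedule at stabilisation.** Two of its eleven rows are marked there: weight, height and BMI, and resource consumption. The visit exists, but no questionnaire is attached to it. The Procedure sentence is too broad in the other direction as well. It places biological assessments at all five times, whereas Table 1 has the nutritional markers at inclusion, weight normalisation and 12 months only.

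**Step 4: ask whether another scheduled score could stand in.** The Procedure section states when care begins to differ: "At the end of the first period, patients start to receive treatment according to their randomisation arm until the weight normalization is reached". In time order:

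1. Inclusion: baseline score (Table 1: x).
2. Period 1: same care in both arms, allocation known to the family.
3. Stabilisation: end of identical care (Table 1: blank).
4. Period 2: day care or continued inpatient care.
5. Weight normalisation: next score (Table 1: x).

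The score at step 5 follows step 4, so it cannot separate expectation from care. Under Table 1 no score after inclusion precedes the divergence.

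**Step 5: check the other endpoint of the objective.** Duration before stabilisation needs the date of inclusion and the date on which stabilisation is reached. Both are visits in Table 1, so this part can be answered.

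**The case against.** The strongest reply is that nothing in the document gives Table 1 precedence. The objective and the Procedure sentence both put the measurement at stabilisation, the full protocol and Figure 1 are not shown, and one empty cell does not show what the centre collects. This stands in part. It means that the document contradicts itself, not that the score is known to be missing. It does not remove the problem. The Procedure sentence names no instrument and is also out of step with Table 1 on biology, and Table 1 is the only schedule in the article that sets instruments against visits. Nor is this a detail left to a fuller document, because the article states the timing and does so inconsistently.

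Four stronger readings may tempt a reader, and the text does not support them:

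- **The whole fourth objective is lost.** It is not, because the duration endpoint needs only dates.
- **The second objective promises biology at 6 months that Table 1 omits.** That objective gives one shared list of time points for several domains together. It does not say that each domain is measured at each time.
- **The inclusion questionnaire may be completed after the family knows the arm.** The article does not say so. The order of questionnaire and disclosure is a detail that a condensed article may leave out.
- **The HAQ-11S is also needed at stabilisation.** Table 1 groups it under motivation, but the Secondary outcomes section describes it as measuring the working relationship between patient and team. The objective names motivation.

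**Conclusion.** The contradiction is real and should be resolved. Table 1 omits motivation to change at stabilisation, against the fourth objective and the Procedure text. If Table 1 is followed, none of the 88 planned children would have the stabilisation score, and the motivation half of that objective could not be assessed. If the Procedure sentence is followed, the score exists and only the table is wrong. The article does not settle which applies, so the count of none out of 88 is conditional and should not be read as a fact about the trial.

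The conclusion assumes that the table row is intact, as Step 2 indicates, and that the figure not shown does not resolve the matter. The reach is limited to one endpoint of one secondary objective. BMI at 12 months, the margin, the sample size and the non-inferiority conclusion are untouched.

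**What to change.** 1. Reconcile the fourth objective, the closing sentence of the Procedure section and Table 1 by marking the two-item Motivation questionnaire at stabilisation, in Table 1 and in the eCRF. Because Table 1 places it in one row with the HAQ-11S, split that row so that only the Motivation questionnaire gains the extra mark.
2. State the analysis: compare the arms on the stabilisation motivation score, adjusted for the inclusion score.
3. Reword the general sentence in the Procedure section so that it agrees with Table 1 on which assessments are done at which visit.
4. The Discussion says the trial began before the pandemic, so first check whether the eCRF already collects the score at stabilisation. If it does, only the table needs correcting. If it does not, report how many children passed that visit without it.

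The cost is two self-report items at a visit that already takes place, the matching eCRF fields and a small amendment to the schedule.

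### Table 1 schedules no motivation score at somatic stabilisation, although objective 4 names that time point and the Procedure text places psychometric assessments there

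*Protocol article*

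**What the plan says.** Three places in the protocol article bear on this.

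- **Background, fourth specific objective.** The effect of the prospect of discharge to day care on the initial inpatient phase is to be assessed by "duration before somatic stabilisation, motivation to change) at inclusion and somatic stabilisation".
- **Procedure, last paragraph.** "Clinical, biological and psychometric assessments are done at baseline, at somatic stabilisation, at reaching weight normalisation, at 6 months and 12 months" after inclusion.
- **Measures, Table 1.** The row for motivation to change, "HAQ-11S, Motivation questionnaire", is marked at inclusion, weight normalisation, 6 months and 12 months. The Stabilisation cell is empty.

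On the instrument, Secondary outcomes states: "The Motivation Questionnaire will assess the importance of change and the perceived ability to change". It has two items, each rated 0 to 10. On disclosure, the Procedure section states: "Children and parents are informed of the result of the randomisation by the investigator". Period 1 care is described as the same for all children, and the arms separate only at its end.

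**The concern.** The objective concerns an effect of expectation. Families know the allocation while every child is still in full-time inpatient care, so any effect on motivation during period 1 should show by the end of that period. The objective names that time point, and the measure-by-measure schedule has no motivation score there.

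If the schedule is applied as printed, the next motivation scores come at weight normalisation or 6 months. By then one arm will generally have continued as inpatients while the other has had day care with a return to home and school. A difference between arms would then reflect the care received as well as the prospect of it. A score not taken at stabilisation cannot be recovered afterwards.

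**Working it through.** The plan gives no figure on this point, so the check is mainly a comparison of texts.

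**Step 1. Read the Table 1 rows against the five column headings.**

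| Row | Inclusion | Stabilisation | Weight normalisation | 6 months | 12 months |
|---|---|---|---|---|---|
| Weight, height, BMI | x | x | x | x | x |
| HAQ-11S, Motivation questionnaire | x | blank | x | x | x |
| Resource consumption | blank | x | x | x | x |

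The first and third rows show that the Stabilisation column survived text extraction. The blank in the motivation row is therefore not a lost column. Only these two other rows carry a mark at stabilisation.

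**Step 2. Compare the three sources on one question: is motivation scored at stabilisation?**

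- Objective 4: yes, named explicitly.
- Procedure text: yes, under psychometric assessments.
- Table 1: no.

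**Step 3. Ask whether the Procedure text settles it.** It does not clearly do so. The same sentence places biological assessments at all five times, whereas Table 1 marks the nutritional markers only at inclusion, weight normalisation and 12 months. The sentence is a general summary that departs from Table 1 in more than one place. Data collection and management says a checklist of measures is completed at each visit. If that checklist was built from Table 1, the motivation score will not be collected at stabilisation.

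**Step 4. Take the two parts of objective 4 separately.**

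- Duration: stabilisation is a defined event (inpatient care is "ongoing until somatic stabilisation, which is defined as: BMI over the 3^rd^ percentile, disappearance of somatic severity criteria for undernutrition") with its own visit, and the Economic evaluation section says the centre's database records admissions. This part is measurable under either reading.
- Motivation: scored at stabilisation under the Procedure text, not under Table 1.

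Table 1 alone therefore supports one of the two parts; the Procedure text supports both.

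**Step 5. What the missing comparison could deliver.** The half-width of the 95% confidence interval for a difference between arms is about 1.99 × SD × √(2/n). The 40 and 44 per arm come from the Sample size section. The SD of a 0 to 10 item is not given, so 2 to 3 points is an assumption.

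- SD 2, n = 44: 1.99 × 2 × √(2/44) = 0.85
- SD 2.5, n = 44: 1.99 × 2.5 × √(2/44) = 1.06
- SD 3, n = 40: 1.99 × 3 × √(2/40) = 1.33

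These figures describe a comparison that could be made. They do not measure the size of the inconsistency.

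**The case against.** The strongest reply is that this is a contradiction and not a plain omission. Two of the three places put the measure at stabilisation. The article condenses a full protocol that is not shown, and the flowchart is not visible here. The score may well be collected. That stands: the consequence follows only if Table 1 governs, and the documents do not say which source does.

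Several stronger readings are tempting, and the documents do not support them.

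- A reader might infer that objective 4 as a whole cannot be assessed. Its duration part needs no questionnaire.
- A reader might infer that the first score after allocation always comes after the whole of period 2. Weight normalisation is event-driven and 6 months is fixed, so a child not yet normalised at 6 months would be scored then. That score may still be affected by the different care in period 2.
- A reader might infer that the inclusion score is worthless for this objective. The article does not say whether it is taken before or after families learn the allocation. Taken before, it is a baseline. Taken just after, a difference between randomised arms would reflect an immediate effect of the prospect, though not its effect over the inpatient phase. The article's naming of inclusion is not shown to be an error.
- A reader might infer that families are told the allocation in order to serve objective 4. No reason is stated.

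**Conclusion.** The point holds as an internal inconsistency with a practical consequence. Table 1 disagrees with objective 4 and with the Procedure text on whether motivation is scored at stabilisation. If Table 1 is followed, the motivation part of one secondary objective lacks its named score after allocation, at the point where the arms differ by design only in the prospect of day care. The blank cell and the disagreement are certain; that data will be lost is conditional on which source the case report form follows. The primary outcome, the non-inferiority test and the sample size are untouched. It is worth correcting because the correction is cheap and a missed score is not recoverable.

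**What to change.** Reconcile objective 4, the Procedure text and Table 1 by marking the two-item Motivation Questionnaire under Stabilisation in Table 1, to be completed before the arms diverge. Compare the arms on that score, adjusting for the inclusion score if it was taken before the allocation was disclosed. Check that the visit checklist and the eCRF carry the form.

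The HAQ-11S may be added because it shares the row, but objective 4 names motivation only, and the article describes the HAQ-11S as a measure of collaboration between patient and team.

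Cost: one short form at a visit that already takes place. Children already past stabilisation will lack the score, and the report should say which children the comparison covers.
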